### Strategies to improve adherence to interventions {11c}

Additional services will be provided for participants through WeChat or phone to arrange the treatment time to enhance their adherence. The monitor or principal researcher will visit every study site monthly to ascertain that all aspects of the program are being followed and that the trial is being carried out in accordance with the provisions of the drug clinical trial quality management good clinical practice (GCP). During the monitoring visit, the monitor will check the CRF for subjects in the trial to confirm that all items have been completed and that the data are being obtained according to the protocol. The monitor will also check that the CRF data are consistent with the clinical records or the original data.

### Relevant concomitant care permitted or prohibited during the trial {11d}

Other treatments that may affect the outcomes of the study, such as traditional Chinese medicine, acupuncture, and massage, are prohibited during the trial.

### Provisions for post-trial care {30}

Participants may quit the study at their guardians’ discretion or defer to the supervisory team if they are not responding well to treatment. They will be followed up and receive appropriate therapy free of charge after they leave the study.

### Outcomes {12}

Endpoint measurements will be performed before the treatment (baseline survey; month 0) and at 7 months (M 7), 12 months (M 12), and 24 months (M 24) after the starting point.

#### Primary endpoint

The primary endpoint of the trial is the mean change in AHI from baseline (M 0) to the primary endpoint (M 7), because PSG is still the gold criterion for diagnosing OSAHS. All subjects will undergo attended overnight PSG in a hospitalized ward. They will go to bed at their usual sleeping time and sleep for at least 6 h to ensure PSG monitoring time. A reduction in airflow of more than 90% compared to that preceding sleep breathing is considered to be an obstructive apnea. A hypopnea is defined as a reduction in airflow of more than 30%, accompanied with an oxygen desaturation of ≥ 3% and/or an arousal. A duration of the obstructive apnea or hypopnea equal to or greater than two respiratory cycles is defined as an obstructive event. The definition of AHI is the number of obstructive events per hour. The analysis will include mixed events but not central events.

#### Secondary endpoints

The secondary endpoints will consist of the lowest oxyhemoglobin saturation (LSaO_2_), apnea index, and hypopnea index assessed by PSG, subjective symptoms (assessed by the OSA-20 questionnaire), cephalometric measurements, and morphologic analysis of the UA.

#### Subjective symptoms

Subjective symptoms will be assessed according to the OSA-20 questionnaire. OSA-20 includes 20 questions divided into five domains: sleep interference, physical suffering, emotional disorder, diurnal problems, and guardian concern. These questions are graded on a scale of 1 to 7 applying an ordinal Likert scoring system. Guardians will complete the questionnaire without help to ensure its reliability and validity. A total score ranging from 20 to 140 points will be associated with quality of life.

#### LSaO_2_

The lowest oxyhemoglobin saturation will be assessed according to PSG.

#### Cephalometric measurements

Lateral cephalometric radiographs will be taken for all the subjects at the intercuspal occlusion and then traced and digitized using the software Dolphin Imaging (Dolphin Imaging & Management Solutions Corporation, Chatsworth, CA, USA). The cephalometric measurements are presented in Fig. 3. The measurement items are as follows: SNA, angular indicator for assessment of maxillary protrusion; SNB, angular indicator for assessment of mandibular protrusion; ANB, angular indicator for assessment of the sagittal relationship between the jaws; MP-FH, angle between the mandibular plane and Frankfort plane; MP-SN, angle between the mandibular plane and SN plane; UI-SN, angular indicator for assessment of upper anterior teeth protrusion; LI-MP, angular indicator for assessment of lower anterior teeth protrusion; UL-Ep, distance between upper lip and the aesthetic plane; LL-Ep, distance between lower lip and the aesthetic plane.

**Fig. 3 Fig3:**
[figure not shown]
Cephalometric landmarks and indicators. *S* sella, *N* nasion, *Po* porion, *Or* orbitale, A subspinale, B supramental, *Ui* upper incisor, *Uir* upper incisor root, *Li* lower incisor, *Lir* lower incisor root, *Me* menton, *Go* gonion, *UL* upper lip anterior, *LL* lower lip anterior, *FH* the Frankfort plane, *MnP* the mandibular plane, *Ep* the aesthetic plane, *UL-Ep* distance between UL and the aesthetic plane, *LL-Ep* distance between LL and the aesthetic plane

#### Morphologic analysis of UA

Cone beam computed tomography (CBCT) of subjects will be performed at the Radiology Department of Shanghai Stomatological Hospital according to the standard protocol. During the scanning, subjects will be positioned in orthostatism, with the Frankfort plane parallel to the floor. The images will be digitized in Digital Imaging and Communications in Medicine (DICOM) files and then imported into Dolphin software for anatomic landmark localization and UA measurements. Two orthodontists will be trained as analysts and will perform the localization and UA measurements as presented in Fig. 4. The analyst will be blinded to patients’ information during the measurements.

**Fig. 4 Fig4:**
[figure not shown]
Morphologic analysis of upper airway. **a** Localization planes of CBCT images. **b** Segmented upper airway. **c** Minimum cross-sectional area (*CSAm*) on the axial slice of the CBCT image. *PNS* posterior nasal spine, *TUV* tip of the uvula, *TEP* tip of the epiglottis, *ATCV* anteroinferior aspect of the vertebral body of the third cervical vertebra, *AP* anteroposterior

### Participant timeline {13}

The clinical trial schedule is shown in Table 1.

### Sample size {14}

The sample size was calculated using SAS 9.4 (SAS Institute Inc., Cary, NC, USA) in this study. Our expectation hypothesis is that the intervention may decrease subjects’ AHI. In a study reported in 2016, the AHI score decreased by 0.8 in children with mild OSAHS who received AT, while it increased by 2.1 in the watchful waiting group (*P* < 0.05) [44]. Another non-randomized study reported that the average AHI of children decreased by 2.0, 15, and 3.7 after medical therapy, AT, and orthodontic treatment respectively [45]. If 80 eligible subjects in each group are expected, we will be able to detect an effect value of 0.4 (the average decreasing of AHI among groups was 2.9) at a power of 80% and a 5% significance level. In consideration of a potential dropout rate of approximately 10%, a total sample size of 352 subjects will be required in this study.

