## Statistical methods

### Statistical methods for primary and secondary outcomes {20a}

Statistical analysis will be conducted using IBM SPSS Statistics (version 22.0). Descriptive analysis will be performed for all of our variates. The analysis set will consist of the intention-to-treat (ITT) set, per protocol (PP) set, and safety set. All subjects will be included in the ITT set after randomization regardless of whether they received the treatment or not. Subjects who complete treatment sessions (M 0 to M 7) without any major violation to the trial procedure will be included in the PP set. Participants who receive treatment will be included in the safety set for safety analysis. The significance level will be set so that *P* < 0.05 will be considered significant.

The primary endpoint of this study is the change in AHI from M 0 to M 7. Intergroup comparisons will be performed using an analysis of covariance (ANCOVA) to adjust for gender, obesity status, and baseline AHI. The outcomes will be mainly analyzed using the PP set. Linear regression will be used to evaluate the correlation between observed differences of AHI and the potential prognostic factors, such as gender, BMI, neck size, and research site.

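### With 80 children per arm, an effect of 0.4 has about 71% power if the comparison is two-sided, pairwise and unadjusted, and the accompanying 2.9 is not a contrast between arms of this trial

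*Protocol article*

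**What the plan says.** The section Sample size {14} of the protocol article gives the whole justification in a few sentences. The hypothesis is that treatment may lower AHI. Two sources follow. In a 2016 study, "the AHI score decreased by 0.8 in children with mild OSAHS who received AT, while it increased by 2.1 in the watchful waiting group". In a non-randomized study, mean AHI fell by 2.0, 15 and 3.7 after medical therapy, AT and orthodontic treatment.

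The conclusion is: "If 80 eligible subjects in each group are expected, we will be able to detect an effect value of 0.4", glossed in parentheses as "the average decreasing of AHI among groups was 2.9", "at a power of 80% and a 5% significance level". The article does not say whether 0.4 is a standardized difference between two arms (Cohen's d) or a spread across four arms (Cohen's f). It also gives no test, sidedness or SD.

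The section on statistical methods {20a} says "The significance level will be set so that" P < 0.05 counts as significant, again without sidedness. It plans an ANCOVA for the intergroup comparisons of AHI change from M 0 to M 7, adjusted for gender, obesity status and baseline AHI. The four arms (Trial design {8}; choice of comparators {6b}) are drug, surgery, orthodontics, and surgery followed by orthodontics.

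**The concern.** The number per arm, the effect and the power are published together, so a reader can check whether they agree. Under the test most readers would assume, they do not. The AHI figure given to explain the effect also appears to come from a comparison that this trial does not make.

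This affects how the results will be read. A non-significant difference between two arms would be judged against a claimed 80% power. If the true figure is nearer 71%, the chance of missing an effect of 0.4 SD is about 29% rather than 20%, and a null result is weaker evidence of no difference than it seems. Nor can a reader tell which contrast, or what AHI difference, the trial was sized to find.

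**Working it through.** **Inputs from Sample size {14}:** n = 80 per arm, four arms, effect 0.4, power 80%, significance level 5%. The readings below differ only in what the article leaves open.

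**1. Which reading reproduces 80 per arm?** For two arms with standardized difference d, the normal approximation is n = 2(z_α + z_β)²/d², with z_β = 0.842 for 80% power.

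- One-sided 5%: 2(1.645 + 0.842)²/0.16 = 77.3, so 78 per arm. At n = 80, d√(n/2) = 0.4 × √40 = 2.530, and Φ(2.530 − 1.645) = 0.812. The noncentral t gives 0.809. This reproduces the stated figure.
- Two-sided 5%: 2(1.960 + 0.842)²/0.16 = 98.1, so 99 per arm. The noncentral t gives 99.1, so 100. At n = 80, Φ(2.530 − 1.960) = 0.716, and the noncentral t gives 0.710. This does not reproduce it.
- Effect detectable two-sided with 80% power at n = 80: (1.960 + 0.842)/√40 = 0.443. The noncentral t gives 0.446.

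**2. Covariate adjustment, two-sided.** If the covariates correlate with the outcome at ρ, the variance shrinks by 1 − ρ².

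| ρ (assumed) | n per arm for 80% | power at 80 per arm |
|---|---|---|
| 0 | 99 | 71.6% |
| 0.30 | 90 | 75.6% |
| 0.40 | 83 | 78.8% |
| 0.44 | 80 | 80.4% |
| 0.50 | 74 | 83.2% |

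The article gives no value of ρ.

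**3. Four-arm F test, 320 children in total.**

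- If 0.4 is Cohen's f, 72.2 children in total suffice. That is 18.04 per arm, so 19, and 80 per arm would be far more than needed.
- If 0.4 SD is the largest gap between any two arms, power depends on where the four means lie:

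| Pattern of means | f | power |
|---|---|---|
| two extremes, two in the middle | 0.141 | 54% |
| equally spaced | 0.149 | 59% |
| one arm apart from three | 0.173 | 74% |
| two arms apart from two | 0.200 | 86% |

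The f detectable with 80% power is 0.186. Some patterns would therefore reach 80%, but the article specifies none.

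**4. Where could 2.9 come from?**

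- 2016 study, AT versus watchful waiting: 0.8 + 2.1 = 2.9 exactly.
- Second study, differences between arms: 3.7 − 2.0 = 1.7, 15 − 3.7 = 11.3 and 15 − 2.0 = 13. None is 2.9.
- Second study, averages of decreases: (2.0 + 3.7)/2 = 2.85, and (2.0 + 15 + 3.7)/3 = 6.9. The first rounds to 2.9, but it is a mean change within arms, not a difference between them.

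On either match, 2.9 is not a difference between two arms of this trial.

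**The case against.** The strongest reply is that the article never says two-sided, pairwise or unadjusted. A reader might infer that the 80% is simply an arithmetic mistake, and the documents do not support that. The hypothesis is worded as a decrease, and a one-sided 5% test gives 78 per arm and 81% power. The primary analysis already adjusts for baseline AHI. If baseline and M 7 variances are equal (an assumption), the correlation between baseline and change is √((1 − r)/2), where r is the baseline-to-M 7 correlation. That is 0.50 at r = 0.5 and 0.45 at r = 0.6, enough to bring two-sided power to 80%. The four-arm range of 54–86% also contains 80%. Finally, an article may leave such details to a fuller document.

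This makes the 71% conditional, but it does not restore the stated figure. The directional sentence describes change under treatment and does not say which of four active arms should do better. No one-sided test is declared, and a four-group ANCOVA F test has no direction. The adjustment is planned, but no variance gain is claimed in the sample size. The four-arm reading needs a favourable pattern of means that is not given. The objection leaves the 2.9 untouched, except that its origin is inferred from matching sums rather than stated.

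Two further inferences should not be drawn:

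- Dividing 2.9 by 0.4 suggests an SD of 7.25. The article states no SD and does not say that 0.4 was obtained that way, so neither the plausibility of that SD nor a power figure built on it can be held against the plan.
- The total of 352 might seem too small because 320/0.9 = 356. The article says only about 10%. Losing 32 of 352 (9.1%) leaves exactly 80 per arm, so this is not a fault worth raising.

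**Conclusion.** The point holds in conditional form. If the intended comparison is two-sided at 5%, between two arms and without covariate gain, power for 0.4 SD at 80 per arm is about 71%. About 100 per arm (400 evaluable rather than 320) would be needed for 80%, and the effect detectable with 80% power is about 0.45 SD. That is the usual reading of the article's significance rule. The readings that support 80% each need something the article does not declare: a one-sided test, a covariate correlation of about 0.44, or a favourable pattern of four means.

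The second part does not depend on sidedness. The 2.9 matches AT versus watchful waiting, a contrast absent from this trial, and no pair of arms in the second source yields it. The basis for the sample size therefore needs restating, although the number of children need not change.

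**What to change.** Keep 352 and restate what it delivers. Suggested wording: *With 80 evaluable children per arm, a two-sided 5% comparison of two arms has about 71% power for a difference of 0.40 SD and 80% power for about 0.45 SD, before any gain from covariate adjustment.*

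If something else was intended, say so in Sample size {14} and align the statistical methods section {20a}:

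- for a one-sided test, name the test and the direction for each contrast;
- for a covariate-adjusted variance, give the assumed correlation;
- for a four-arm F test, give the effect metric and the pattern of means.

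In every case, replace 2.9 with the target AHI difference between named arms of this trial, together with the SD used.

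The cost is wording only, with no extra children and no change of design. The drawback is that under the suggested wording the stated power becomes less favourable.

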### Concealment mechanism {16b}

The Central Randomization System can be used for the management of participant information and randomization. Prior to signing an informed consent form, this study will be fully explained to subjects and their guardians by researchers at every study site. The basic information of patients will be registered into the Central Randomization System by research assistants. After the baseline survey, the eligible participants will be divided into four groups at random with a ratio of 1:1:1:1.

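### The sample-size allowance covers about 10% dropout only, but the main analysis uses a per-protocol set with further exclusions, so 80 per arm is not what that analysis will have unless total losses stay at or below 9.1%

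*Protocol article*

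**What the plan says.** In the protocol article, Sample size {14} takes 80 children per group as the basis ("If 80 eligible subjects in each group are expected") and says of that number: "we will be able to detect an effect value of 0.4 (the average decreasing of AHI among groups was 2.9". The claimed power is 80%, with significance set at 5%. The section then moves to the number to enrol: "In consideration of a potential dropout rate of approximately 10%, a total sample size of 352 subjects will be required in this study". No other loss is named. Allocation is equal across four groups (Concealment mechanism {16b}), so 352 means 88 per arm.

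Statistical methods for primary and secondary outcomes {20a} defines three analysis sets and names the leading one: "The outcomes will be mainly analyzed using the PP set". Membership of that set is fixed as follows: "Subjects who complete treatment sessions (M 0 to M 7) without any major violation to the trial procedure will be included in the PP set". The ITT set holds every randomised child. Section {20c} fills missing data by last observation carried forward.

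**The concern.** The number behind the power statement and the number entering the main analysis are not the same quantity. The allowance from 80 to 88 per arm is described as dropout. The per-protocol set removes more than dropouts: it also removes children with a major violation, and children who remain under observation but do not complete treatment to month 7. Non-completion partly overlaps with dropout, so only the additional exclusions are uncovered.

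The protocol gives reasons to expect some. Its Discussion names compliance as a challenge, two of the four arms use a removable appliance, and section {11d} prohibits other treatments that may affect outcomes. At stake is whether a reader can take 80 per arm, and the power attached to it, as describing the analysis on which the trial will mainly report.

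**Working it through.** **Inputs.** From Sample size {14}: 80 per arm, effect value 0.4, 80% power, 5% significance, about 10% dropout, 352 in total. From {16b}: 1:1:1:1 allocation. From {20a}: the main analysis is per protocol. Assumed, because the documents give no figure: a further 5%, 10% or 15% excluded from the per-protocol set among children who did not drop out.

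**1. Reproducing 352.** 4 × 80 = 320, and 320 × 1.10 = 352, or 88 per arm. The figure is reproduced exactly.

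**2. What 88 per arm leaves at exactly 10% loss.** 88 × 0.9 = 79.2 per arm (352 × 0.9 = 316.8 in total). Holding 80 would take 80/0.9 = 88.9, so 89 per arm or 356 in total. The gap is 0.8 of a child per arm, or four children randomised.

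**3. Largest total loss that still leaves 80.** 1 − 80/88 = 8/88 = 9.1%. This must cover dropout and every further per-protocol exclusion together.

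**4. Per-protocol number under the assumed range.** n = 88 × 0.9 × (1 − e):

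- e = 5%: 88 × 0.9 × 0.95 = 75.2
- e = 10%: 88 × 0.9 × 0.90 = 71.3
- e = 15%: 88 × 0.9 × 0.85 = 67.3

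**5. Power at those numbers.** The section states neither the effect measure nor whether the test is one- or two-sided. The reading closest to the stated 80% at 80 per arm is a standardised mean difference d = 0.4 between two groups, one-sided 5%, no covariates; it needs 78 per arm. Power comes from the noncentral t distribution with 2n − 2 degrees of freedom and noncentrality 0.4 × √(n/2):

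| Per arm | One-sided | Two-sided |
|---|---|---|
| 80 | 80.9% | 71.0% |
| 79.2 | 80.5% | 70.6% |
| 75.2 | 78.7% | 68.4% |
| 71.3 | 76.8% | 66.0% |
| 67.3 | 74.7% | 63.5% |

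**6. The other reading of 0.4.** As Cohen's f in a four-group analysis of variance, 0.4 needs only 19 per arm for 80% power, and power at 67 per arm is above 99.9%. On that reading the lower per-protocol number does not bring power below 80%.

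**The case against.** Several objections carry weight.

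- **The inflation step.** The protocol says approximately 10%, and 352 leaves exactly 80 per arm at 9.1% loss, which fits that wording. A reader might infer that 352 is a wrong sample size, or that the stated power is missed even when dropout is exactly 10%. The documents do not support either. On the one-sided d = 0.4 reading, 79.2 per arm still gives 80.5%, and the step from 80 costs under half a power point. On the two-sided reading, power is 71% at 80 per arm before any loss, so the inflation step is not the cause. This objection stands.
- **Assumed exclusion rates.** The 5%, 10% and 15% appear nowhere in the documents. They were applied equally to all arms, although drug treatment lasts two months and surgery is a single procedure, so failure to complete treatment is mainly a matter for the two orthodontic arms. The article does not define dropout and might use it loosely for every child who cannot be evaluated. This limits the size of the point. It does not remove the mismatch: on the text as written only dropout is allowed for, and even a loose 10% would leave 79.2.
- **Adjusted analysis.** The planned analysis of covariance adjusts for baseline AHI, gender and obesity, which can recover power. If the covariates correlate 0.3 to 0.5 with the outcome (an assumption), one-sided power is about 80% to 86% at 71.3 per arm and 78% to 85% at 67.3. This stands as a reason to treat the power figures as conditional.
- **ITT set and carried-forward values.** The ITT set can keep up to 88 per arm. Neither it nor carrying values forward returns an excluded child to the per-protocol set, which the article makes the main one.
- **Condensed article.** Detail on expected set sizes may sit in the full protocol. But the article itself states both the sample-size basis and the main analysis set, and as stated they do not fit together.

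**Conclusion.** The point holds as a minor one. The allowance is for dropout of about 10%, while the main analysis set also excludes major violators and retained children who do not complete treatment to month 7. That analysis will have fewer than 80 per arm unless all these losses together stay at or below 9.1%. This follows from the document's own figures and does not depend on how 0.4 is read.

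The size of the shortfall does depend on assumptions. With 10% dropout and a further 5% to 15% excluded, 75 to 67 per arm remain. If 0.4 is a standardised mean difference tested one-sided without covariates, power is about 79% to 75% against 81% at 80 per arm. If it is Cohen's f, power is not in question. The multiplication by 1.10 is a slip of four children in total and does not by itself lose the stated 80%.

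**What to change.** Restate Sample size {14} without enrolling more children: 352 randomised (88 per arm); about 79 per arm with month 7 data at 10% dropout; the expected per-protocol number per arm once major violations and non-completion among retained children are also allowed for, with the assumed rate given; and the power or detectable difference at that per-protocol number. Naming the effect measure and the sidedness in the same sentence would make the figure checkable. The cost is a few words and a slightly less favourable stated number. Enrolment and analysis do not change.
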